### Trial design {8}

The trial is planned as a prospective, randomized, controlled, non-blinded multi-center study to compare “alley” with standard treatment with scope of a superiority study design in two independent indications. Two hundred patients scheduled for THA and 200 patients scheduled for TKA will be independently randomly assigned to the IG or CG. Assessments will be performed at baseline before TJA (*t*_0_), 10 days after TJA (*t*_1_), 1 months after TJA (*t*_2_), 3 months after TJA (*t*_3_), 6 months after TJA (*t*_4_), and 12 months after TJA (*t*_5_).

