#### Sample size calculation for patients with osteoarthritis of the hip

The sample size calculation for patients with osteoarthritis of the hip is based on an average change score of 9 points with a standard deviation of ± 15 points in the total score of HOOS observed in other intervention studies after three months [30, 31]. Based on this data available, an effect of 0.6 can be assumed. With a standard α-risk of 0.05 and a statistical power of 0.8 (1 – β), a sample size of *n* = 61 patients in each group is required to obtain significant differences in Student’s *t*-test for independent variables. This number of cases will be enlarged to consider any potential data missing. Due to observed dropout rates of up to 20% [32], exclusion of patients due to errors in data entry (4%) [33], an approximate across-the-board increase due to the risk of complications due to corona the number of patients to be included is increased to achieve the required sample size at the time of measurement 3 months post-surgery. Therefore, *n* = 100 participants and *n* = 100 controls were supposed to be recruited for the THA evaluation group.

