### Statistical methods

#### Statistical methods for primary and secondary outcomes {20a}

A two-arm evaluation will be performed. In one arm, all patients of the “hip intervention group” and their CG are analyzed. In the other study arm, the evaluation of the “knee intervention group” and their corresponding CG is carried out. A combination of the data from the two study arms is not intended. The statistical analysis is performed separately for patients with TKA and THA by means of mean, median, standard deviation, and quantiles to initially depict the patient collectives and the primary and secondary endpoints descriptively. The Kolmogorov-Smirnov test as well as histograms and QQ-plots are applied to evaluate normal distribution of all continuous variables. Differences at baseline between IG and CG are assessed with Student’s *t*-test for independent variables in case of normally distributed data or with the Mann-Whitney *U* test in case of non-normal distribution. Categorical variables are examined by *χ*^2^ or Fisher’s exact test. If differences are observed, data risk adjustment with logistic regression is applied.

To evaluate outcome differences between the groups, delta values (change scores) are calculated in each group between the adjacent measurement time points (ti-tj, j > i) for each variable. To address our main superiority hypothesis, delta values from baseline to 3 months post-surgery of the IG and CG are statistically examined using Student’s *t*-test for independent variables. Additionally, Cohen’s *d* effect size and its 95% confidence interval will be calculated. Cohen’s *d* is a measure of the effect size for mean difference between two samples regarding interval-scaled variables. Values of *d* = 0.20 represent small, *d* = 0.50 medium, and values from *d* = 0.80 large effect [36]. In the case of non-normally distributed data, the Mann-Whitney *U* test is applied. To investigate differences at the follow-up measurement time points, further *t*-tests were performed. Because of multiple testing, an alpha error correction according to Bonferroni will be applied.

Significant differences between the several measurement times *t*_0_ to *t*_5_ are evaluated with analyses of variance with repeated measures and paired Student’s *t*-test for normally distributed data. The Friedman test and the Wilcoxon test are used in the case of non-normally distributed data.

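### The further follow-up t-tests are corrected by single-step Bonferroni, which is valid but dominated by Holm's step-down procedure at the same error rate

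*Protocol article*

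**What the plan says.** Section {20a} of the Protocol article tests the main hypothesis once per indication: "delta values from baseline to 3 months post-surgery of the IG and CG are statistically examined using Student’s *t*-test for independent variables". It then adds secondary comparisons at other visits: "To investigate differences at the follow-up measurement time points, further *t*-tests were performed". The next sentence reads: "Because of multiple testing, an alpha error correction according to Bonferroni will be applied".

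The section does not list the tests in the family, the number of tests or the per-test threshold. Trial design {8} gives five post-surgical visits: 10 days and 1, 3, 6 and 12 months. If the 3-month visit is reserved for the primary test, four remain.

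The sample size sections size the trial for the 3-month comparison only ("With a standard α-risk of 0.05 and a statistical power of 0.8", from an "average change score of 9 points with a standard deviation of ± 15 points"). No power is claimed for any other visit. The Interim analyses section {21b} has the 3-month results analysed and published first, with a further analysis after twelve months.

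**The concern.** Bonferroni compares every p-value with α/m, where m is the number of tests in the family. Holm orders the p-values and compares the smallest with α/m, the next with α/(m−1), and so on up to α, stopping at the first failure. Each Holm threshold is at least as large as Bonferroni's, and the family-wise error bound is the same. Choosing Bonferroni therefore buys no extra protection.

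The follow-up tests are what would show whether a benefit appears early and lasts to 12 months. The same patients complete HOOS or KOOS at each visit, and the app is used before and after surgery. An effect at several visits at once is therefore plausible, although the article does not assert it. In that case a single-step threshold can make a lasting benefit look patchy across visits.

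**Working it through.** **Is there a plan figure to reproduce?** There is none for the follow-up tests. The only related figure is 61 per group for the 3-month test. From d = 9/15 = 0.6, two-sided α = 0.05 and power 0.80, an exact t calculation needs 45 per group; 61 gives power 0.908. That is a separate matter. Here 61 serves only as the plan's own planning number.

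**Same error control.** Let m0 of the m null hypotheses be true. When Holm first reaches a true null, at most m − m0 hypotheses stand before it, so its threshold is at most α/m0. A wrong rejection therefore requires some true null to have p ≤ α/m0. By the union bound this has probability at most m0 × α/m0 = α, whatever the dependence.

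**Inputs.** From the article: d = 0.6, n = 61 per arm, α = 0.05. Assumed: two-sided tests; m = 4 (10 days, 1, 6 and 12 months); correlation 0.6 between test statistics; equal true effects where an effect is present.

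**Thresholds.** Bonferroni: 0.05/4 = 0.0125 for every test. Holm: 0.05/4 = 0.0125, 0.05/3 = 0.0167, 0.05/2 = 0.025, 0.05.

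**Bonferroni power by hand.** The test statistic has mean d√(n/2) = 0.6 × √30.5 = 3.314. The critical value at 0.0125 two-sided is 2.498. Power = Φ(3.314 − 2.498) = Φ(0.816) = 0.79. The exact t value is 0.78.

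**Holm by simulation** (200,000 sets of four correlated normal test statistics, n = 61, correlation 0.6):

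| True effect | Bonferroni, per true effect | Holm, per true effect |
|---|---|---|
| d = 0.6 at all four visits | 0.79 | 0.86 |
| d = 0.6 at two of four | 0.79 | 0.81 |
| d = 0.6 at one of four | 0.79 | 0.79 |

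With effects at all four visits, the chance of confirming all four is about 0.58 with Bonferroni and 0.77 with Holm.

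**Sensitivity.**
- Correlation 0 to 0.7, d = 0.6 at all four, n = 61: Holm 0.89 down to 0.86, against 0.79.
- d = 0.3 at all four, n = 61: 0.20 against 0.22 to 0.25.
- n = 76 (100 less 24% loss), d = 0.6 at all four: 0.885 against 0.93 to 0.95.
- n = 76, d = 0.5 at all four, correlation 0.6: 0.72 against 0.80.
- A family of 40 tests with four real effects of d = 0.5, n = 76, correlation 0.6: 0.444 against 0.448.

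**Checks.** In every scenario the chance of at least one rejection was identical, because the first rejection faces the same α/m. No simulated set had a Bonferroni rejection that Holm missed. With no effect anywhere, the family-wise error at correlation 0.6 was 0.040 for both. For four independent tests the Bonferroni value is 1 − (1 − 0.0125)⁴ = 0.049.

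**The case against.** The strongest case against is that there is no error to correct. Bonferroni is valid, pre-specified and holds α under any dependence. The primary test is one comparison per indication, the trial is sized for it alone, and no promised power is missed. All of this stands. A reader might infer that the correction is wrong, or that the plan falls short of its stated power at the later visits. The documents support neither.

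A reader might also infer that Holm always rejects more. It rejects at least as much, and gains only once another test in the family has been rejected. The size of the gain rests on a family of four, equal effects and a correlation that the article does not give. Section {20a} computes change scores for every variable, so a much larger family is possible, and there the gain nearly vanishes. This stands too and limits the magnitude, but it does not affect the ordering of the two methods.

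The best practical objection is timing. Under section {21b} the 10-day and 1-month results can be available at the first report, while the 6- and 12-month results are not. Bonferroni decisions are final at once; some Holm decisions would wait. This is real but small: any p-value at or below α/m is rejected under Holm whatever comes later, and later data can only add rejections.

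Finally, Holm has no simple matching simultaneous intervals. The article promises none. It mentions a 95% interval for Cohen's d directly after the primary test and does not clearly extend it to the follow-up tests.

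**Conclusion.** The point holds as an optional improvement. Single-step Bonferroni is valid, but Holm dominates it at the same family-wise error. With four follow-up tests, equal effects at all four, correlation 0.6, and the plan's d = 0.6 and 61 per arm, the loss is about 0.86 − 0.79 = 0.07 in power per comparison. It is about 0.02 with effects at two of four visits, and close to zero with an effect at one visit or in a large family. The chance of finding at least one difference is the same either way. The primary 3-month result is untouched provided that test lies outside the corrected family, which is the natural reading of section {20a} but is not stated. The dominance needs no assumption about the family or the correlation; only the size of the gain does.

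**What to change.** In section {20a}, replace Bonferroni by Holm (step-down Bonferroni) and leave the family of tests unchanged. Add one sentence for the staged reporting in section {21b}: follow-up results reported with the 3-month analysis are declared significant only if p ≤ α/m, and the final Holm decisions for the family are made at the 12-month analysis. The change should be fixed before the follow-up data are analysed.

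The cost is a word and a sentence, with no extra patients or data. Two small downsides remain: some early-visit decisions stay open until 12 months, and simple matching simultaneous intervals are not available.

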## Introduction

### Background and rationale {6a}

Osteoarthritis (OA) is one of the most common disabilities in the elderly. With a lifetime risk of 25% in the population aged 85 years, symptomatic hip OA represents one of the most prevalent diseases [1]. Similarly, the prevalence of knee OA increases with age and can be detected in up to 44% in subjects older than 80 years [2]. OA is a heterogeneous disease evoked by several causes, including local and systemic, genetic, and environmental factors, and is consequently difficult to prevent [3, 4]. When conservative management fails, total joint arthroplasty (TJA) is the treatment of choice for end-stage OA to reliably relieve pain and restore joint function [5, 6]. TJA is considered to be one of the most successful surgical procedures, while it has been shown as a cost-effective intervention for patients who do not benefit from conservative approaches [7]. Worldwide, more than 1 million TJAs are implanted annually [8], and it is expected that in future the number of surgeries will further increase due to demographic changes [3, 9].

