### Objectives {7}

Aim of the study is to evaluate the effectiveness of the eHealth application “alley” as an adjuvant intervention to total joint arthroplasty (TJA) as current gold standard of treatment in patients with knee and hip OA scheduled for surgery. In the presented study design, these two indications will be investigated independently of each other. Nevertheless, for both patients’ groups data collection is carried out via “alley” application. Accordingly, the primary outcome is change from baseline in the functional status measured with the total scores of the Hip Osteoarthritis Outcome Score (HOOS) for patients scheduled for total hip arthroplasty (THA) and the Knee injury and Osteoarthritis Outcome Score (KOOS) for patients scheduled for total knee arthroplasty (TKA).

The primary hypothesis is that the pre- and postoperative adjuvant use of the eHealth application “alley” (intervention group, IG) leads to improved functional outcome 3 months after TJA in patients with knee or hip OA compared to their equivalent control group (CG) that did not use the application. In this research, the overall effect of the application as complex intervention will be evaluated as standalone entity. Individual sub-questions on the subject of health literacy or in which format information should be administered to patients are not evaluated. Our secondary hypotheses are that the eHealth application will further improve pain, quality of life, depression and anxiety, optimistic mood, and risk of falling.

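### The t0 to t5 tests examine change over time, not app versus control; the longitudinal analysis should carry an arm-by-visit term

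*Protocol article*

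**What the plan says.** Section {20a} of the protocol article has two separate parts that bear on this point.

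The first concerns the arms. It begins: "To evaluate outcome differences between the groups, delta values (change scores) are calculated in each group between the adjacent measurement time points". For the main hypothesis, "delta values from baseline to 3 months post-surgery of the IG and CG are statistically examined using Student’s *t*-test for independent variables", with Mann-Whitney U if the data are not normal. Cohen's d with a 95% confidence interval is added. For later visits, "To investigate differences at the follow-up measurement time points, further *t*-tests were performed", followed by a Bonferroni correction.

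The second is the closing paragraph, which concerns time. It states: "Significant differences between the several measurement times *t*_0_ to *t*_5_ are evaluated with analyses of variance with repeated measures and paired Student’s *t*-test for normally" (that is, for the normal case). It mentions neither arm nor an interaction. For other data, "The Friedman test and the Wilcoxon test are used in the case of non-normally distributed data".

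The hypotheses are in Objectives {7}. The primary one compares the intervention group (IG) with the control group (CG) at 3 months. For the rest, "Our secondary hypotheses are that the eHealth application will further improve pain, quality of life, depression and anxiety, optimistic mood, and risk of falling". Both arms receive the operation, and Background {6a} states that "total joint arthroplasty (TJA) is the treatment of choice for end-stage OA to reliably relieve pain and restore joint function".

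**The concern.** The tests in the closing paragraph have as their null hypothesis that scores do not differ between visits. Every hypothesis in Objectives {7} is about the app, and none asks whether patients change after arthroplasty. Since both arms have a joint replaced, that null is expected to be false in both arms for function and pain, whatever the app does.

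The non-normal alternatives point to a time-only reading of the ANOVA as well. Friedman and Wilcoxon are the counterparts of a one-way within-patient ANOVA and of the paired t-test, and neither has a place for the arm. If an interaction was intended in the ANOVA, the rank-based fallback would not test it.

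What is at stake is limited. The joint analysis of all six visits, as worded, cannot tell a useful app from a useless one, although the data to do so are collected. A significant course over time could then be misread as supporting the app.

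**Working it through.** **Inputs.** From Sample size {14}: a change of 9 points, SD 15, 61 evaluable and 100 recruited per group, alpha 0.05 (taken as two-sided). From Table 2: six visits for HOOS/KOOS. Assumptions: both arms share the same course (no app effect), within-patient correlation is 0.5, and the SD is 15 at each visit. The SD of change is then 15 × √(2 × (1 − 0.5)) = 15. The protocol gives no size for the change after surgery. It uses 9/15 as the effect size for comparing two groups; using 9 points as a common within-arm change is an assumption, so a range is shown.

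**The plan's own figure.** The stated 61 per group does not reproduce. With d = 0.6, two-sided alpha 0.05 and power 0.80, the exact t calculation gives 45 per group; 61 gives about 91% power. This does not affect the present point, and 61 is used below as the planned evaluable number.

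**Paired t-test, t0 to t3, within one arm.** The noncentrality is (change/15) × √n, compared with the two-sided 5% critical value (2.00 on 60 df).

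| Common change | Noncentrality, n = 61 | P(significant), n = 61 | P(significant), n = 100 |
|---|---|---|---|
| 3 | 0.2 × 7.81 = 1.56 | 34% | 51% |
| 5 | 0.333 × 7.81 = 2.60 | 73% | 91% |
| 9 | 0.6 × 7.81 = 4.69 | 99.6% | >99.9% |

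Six visits give 6 × 5 / 2 = 15 pairs. With Bonferroni over all 15 (an assumed number of tests), the 9-point change at n = 61 is still significant in 94% of trials. Correcting alpha does not change which question the test answers.

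**Simulation with no app effect.** 61 per arm, 3000 trials, the same course in both arms, 9 points of improvement by t3:

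| Test | Significant |
|---|---|
| Paired t, t0 to t3, one arm | 99.6% |
| Wilcoxon, t0 to t3, one arm | 99.6% |
| Friedman, one arm | 100% |
| ANOVA, time effect | 100% |
| ANOVA, arm-by-time | 5.1% |
| Planned between-arm t-test on change, t0 to t3 | 4.7% |

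With no change over time, all of these tests stay near 5%.

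**Can the same data answer the app question?** Take an app effect of 0, 3, 6, 9, 9, 9 points over the six visits. The squared deviations from its mean of 6 sum to 36 + 9 + 0 + 9 + 9 + 9 = 72. The within-patient error variance is 225 × (1 − 0.5) = 112.5. The arm-by-time noncentrality is (n/2) × 72/112.5, which is 19.5 at n = 61 and 32 at n = 100 per arm. Power is about 95% and 99.7%. The time effect rejects in 100% of simulated trials with or without this app effect.

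**The case against.** The strongest reply is that the app question is already answered elsewhere in the section. Change scores are formed for each variable expressly to compare the groups, IG is tested against CG at 3 months, further t-tests follow for the later visits, and Bonferroni is applied. An IG minus CG difference in the change between two visits is itself an arm-by-time contrast. This stands. A reader might infer that the plan has no between-arm comparison of the recovery course, or that its efficacy conclusions rest on the time tests. The documents support neither.

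Second, the protocol describes the closing paragraph as a comparison of measurement times and never says that a time effect will count for the app. Describing the post-operative course is legitimate. This stands too, although the tests are written as significance tests and not placed with the descriptive statistics.

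Third, a repeated-measures ANOVA can carry an arm factor and its interaction, and an article may leave that detail to a fuller document. This stands for the ANOVA. It does not rescue the paired t, Friedman and Wilcoxon tests, which the article names and which cannot contain the arm.

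Fourth, near-certain significance is not general. It depends on a clear shift after surgery, and a 3-point change gives only 34% at n = 61. Dispositional optimism may hardly move. A reader might also infer that running the tests by arm will often yield significance in IG but not in CG. With p the chance of significance in one arm, exactly one arm is significant with probability 2p(1 − p). That is 45% to 50% for common changes of 0.2 to 0.3 SD at n = 61, but only 2 × 0.996 × 0.004 = 0.8% at the 9-point change. The two problems cannot both apply to the same outcome and interval, and the article does not say that the paired tests are run by arm.

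**Conclusion.** The point holds in a limited form. The t0 to t5 tests are worded as tests of change over time and match no stated hypothesis. For outcomes that arthroplasty clearly changes, chiefly HOOS/KOOS and pain, their significance says nothing about the app. The 99.6% to 100% rejection rates with no app effect rest on an assumed common 9-point change with SD 15 and 61 per arm; the simulated rates also assume a within-patient correlation of 0.5. Smaller changes give much lower figures.

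The primary between-arm t-test and the further between-arm tests on change scores keep their meaning; the 3-month test stays at about 5% error in the simulation. This is a worthwhile improvement to a secondary analysis. It does not threaten the primary result.

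**What to change.** In section {20a}, for each indication and each continuous outcome measured repeatedly, make the longitudinal inferential analysis a repeated-measures mixed model with arm, visit, arm-by-visit and baseline score (the last where a baseline exists; Table 2 shows none for patient satisfaction). Test arm-by-visit, and report IG minus CG with a 95% confidence interval at each visit. Keep the 3-month between-arm comparison as primary.

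State that the within-patient time analyses (ANOVA time effect, paired t, Friedman, Wilcoxon) describe the post-operative course and are not evidence for the app.

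The cost is wording only, with no added patients, visits or questionnaires. A covariance structure has to be stated, and within-arm p-values cease to be inferential results.

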#### Interim analyses {21b}

After 3-month post-surgery, the main analysis will be performed to address the primary research question. The analysis will be conducted by a blinded statistician and the results will be published. Main analysis will be conducted after twelve months by the same blinded statistician.

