### Assignment of interventions: blinding

#### Who will be blinded {17a}

Neither patients nor medical stuff are blind to the intervention. Patients know whether they are IG or CG by receiving educational content or just receiving questionnaires by the app. Medical stuff will receive information on patients` medical history only from patients of the IG. Therefore, blinding during the study is not possible. However, statistical analysis is performed by a blinded analyst.

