#### Procedure for unblinding if needed {17b}

Not applicable. No unblinding necessary, as trial participants and care providers are not blinded. Unblinding of the data analyst is not intended.

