## Trial status

In July 2021, the first patients were included in selected study sites to evaluate the proposed recruitment management and functionality of the application according to our ethical approved study protocol (ver. 2 from 12 May 2021). Active patient recruitment by all study sites is conducted from 01 September 2021 till 30 February 2022, followed by a maximum of 12-month follow-up.

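### The 12-month analysis cannot be done by the same blinded statistician once the 3-month result has been published by arm

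*Protocol article*

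**What the plan says.** Interim analyses {21b} sets out three steps in order:

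- 3-month analysis: "After 3-month post-surgery, the main analysis will be performed to address the primary research question".
- Publication: "The analysis will be conducted by a blinded statistician and the results will be published".
- 12-month analysis: "Main analysis will be conducted after twelve months by the same blinded statistician".

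Who will be blinded {17a} says of patients and staff: "Neither patients nor medical stuff are blind to the intervention". It then makes the analyst the exception: "However, statistical analysis is performed by a blinded analyst". Procedure for unblinding if needed {17b} adds: "Unblinding of the data analyst is not intended".

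Statistical methods {20a} makes the choice of test depend on a distribution check. The fallback is worded "In the case of non-normally distributed data, the Mann-Whitney" *U* test. Adjustment is applied only if the arms are found to differ at baseline. Methods for additional analyses {20b} has a second conditional adjustment, tied to sex, age and secondary diseases.

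**The concern.** Patients and clinical staff know the allocation, and the outcomes are self-reported, so analyst blinding is the only masking the trial claims. It matters most where the plan leaves a decision until the data have been seen. For the follow-up comparisons that protection is promised, but the planned sequence removes it. A reader of the 12-month paper would be told that the test and the adjustment were chosen blind, when the analyst already knew which arm was ahead at 3 months. The 6- and 12-month results are the ones a reader would use to judge whether a 3-month effect persists.

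**Working it through.** The plan gives no figure to reproduce here. The check sets its statements side by side and adds calendar arithmetic.

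**1. What the publication reveals.** Under {20a} the primary test compares the baseline-to-3-month change of intervention and control, with Cohen's *d* and its 95% confidence interval, separately for hip and knee. Group descriptives (means, medians, SDs, quantiles) are also planned. A superiority result must name the arms, so after publication its producer knows direction and size for each joint.

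**2. Whether masked labels could survive.** {20a} plans change scores between measurement points and repeated-measures ANOVA over *t*0 to *t*5. The 12-month dataset therefore contains the same patients' *t*0 and *t*3 scores. Computing the *t*0-to-*t*3 change under a masked label reproduces one of the two published arm results, because the data are the same. New codes do not prevent this unless *t*0 and *t*3 are withheld, and the planned analyses need them.

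**3. Whether another section repairs it.** The article describes no second analyst and no follow-up plan locked before the 3-month result. {17b} only says that analyst unblinding is not intended.

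**4. Which decisions remain open.**

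| Decision | Trigger in the plan | Still open after 3 months? |
|---|---|---|
| *t*-test or Mann-Whitney at 6 and 12 months | Kolmogorov-Smirnov test, histograms, QQ plots | Yes: new data, and the plots are judged by eye |
| Adjustment under {20a} | Arm differences at baseline | Largely no: *t*0 data were already examined at 3 months |
| Adjustment under {20b} | Significant differences by sex, age, secondary diseases | Not tied to a time point, so not excluded |

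**5. Calendar.** Trial status reads: "Active patient recruitment by all study sites is conducted from 01 September 2021 till 30 February 2022, followed by a maximum of 12-month follow-up". The closing date does not exist and is taken as 28 February 2022. The wait from recruitment to surgery is not fixed, so 14 to 120 days is assumed.

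- Last *t*3 = 28 Feb 2022 + wait + 3 months: 14 June 2022 (14 days) to 28 September 2022 (120 days).
- Last *t*5 = 28 Feb 2022 + wait + 12 months: 14 March 2023 to 28 June 2023.
- Gap = 12 − 3 = 9 months (273 or 274 days), whatever the wait.
- First main-phase *t*5 = 1 Sep 2021 + wait + 12 months: 15 September 2022 (14 days) to 30 December 2022 (120 days). With equal waits this is 93 to 94 days after the last *t*3. With unequal waits the gap runs from −13 to +199 days.

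So the 3-month data can be complete about 9 months before the 12-month data are, which leaves room for the published order. The dates do not show when publication falls relative to the first *t*5 survey.

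**The case against.** The strongest reply is that little is at risk. The primary hypothesis concerns 3 months and is tested once, before any publication, and reporting a primary result while follow-up continues is not an error. The choice between *t*-test and Mann-Whitney depends on distributional shape and not on which arm is ahead. The {20a} adjustment trigger uses baseline data already seen, and {20a} names further *t*-tests with Bonferroni correction for follow-up. A separate analysis plan may fix the rest. All of this stands as a limit on size. It does not make the sentence in {21b} true: the protocol asserts a blinded 12-month analysis, and a separate plan could lock the choices but could not restore blinding after publication by arm.

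Three stronger readings are tempting and are not supported:

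- A reader might infer that the result is published before any main-phase patient reaches 12 months. No publication date is given, so no share of outstanding *t*5 surveys can be stated.
- A reader might infer that the published result changes patients' later answers. No section plans to send results to patients or sites, Dissemination plans {31a} mentions journals, and patients already know their arm.
- A reader might take the section heading to mean that the 3-month analysis is an interim look that spends alpha. It is the final test of the primary hypothesis.

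**Conclusion.** The point holds in limited form. Publication by arm, followed by a 12-month analysis by the same person, contradicts the statements that this person is blinded and is not to be unblinded. The reach is the 6- and 12-month comparisons in both the hip and knee cohorts: mainly the part of the test choice judged from plots, and any adjustment not settled at 3 months. The primary test is untouched. No bias in a follow-up estimate can be calculated from the documents, and none is claimed.

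Two assumptions carry the conclusion. The steps in {21b} happen in the order written; if disclosure of the arms and publication waited until the 12-month analysis was finished, blinding could hold. The 6-month comparison, which has no analysis date of its own, is taken to be made after the 3-month result is known. The contradiction should be corrected because the statement is wrong as written and the remedy is cheap.

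**What to change.** In {21b}, state that the choice of test and the adjustment rules for the 6- and 12-month comparisons are finalised and dated before the arm codes are revealed for the 3-month result, and are then run unchanged. Delete *blinded* for the 12-month analysis, or assign it to an existing analyst who has not been exposed to the 3-month result. Amend {17a} and {17b} to match: analyst blinding covers the 3-month analysis, and the arms become known to that analyst when the result is reported. The same edit can separate the two analyses now both called main, naming the first as primary and the second as follow-up.

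The cost is wording, plus writing the follow-up program some months earlier. If the same analyst is kept, the claim of a blinded 12-month analysis is given up. No patients, visits or procedures are added, and publication of the 3-month result can go ahead.
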